### Setting

The 8-week group-based IPMP will be held in one nursing home in Hong Kong.

### Samples

#### Participants

The participants will be recruited from one nursing home in Hong Kong. The home-in-charge nurse will be approached and invited to participate in the study. Older adults in the nursing home who are interested to participate will be recruited according to the inclusion criteria. The present study will be a pilot study with 30 participants. Inclusion criteria are older adults aged ≥60, who scored ≥6 in the Abbreviated Mental Test [19], have been experiencing non-malignant physical pain or discomfort either all the time or on and off for more than three months, scored ≥1 in the frailty index [20], and are able to speak and understand Cantonese. Exclusion criteria are those with cognitive impairment and a history of mental disorders, and those with cancer and currently on cancer treatment, since the present study is for older adults with non-malignant pain. As this program involves physical activities, those suffering from conditions that limit safe participation will be excluded. Examples include those who have had a fracture or undergone surgery in the past two months, those with severe chronic obstructive pulmonary disease, acute stroke, and acute myocardial infarction. The ratio of participants to PVs is 1:1. PVs who have not been paired with participants will be responsible for making overall observations during the sessions. Participants and PVs will also be matched according to gender and dialect. Since it is essential that actions be repeated in response to stable cues to become a habit, the participants will be accompanied by the same PV during the study [21].

#### Peer volunteers

We are collaborating with the Institute of Active Ageing (IAA), which is hosted by the Faculty of Health and Social Sciences of the Hong Kong Polytechnic University. The IAA is dedicated to delivering innovative educational programs to promote active aging and the view of older adults as important contributors to society. It provides many opportunities for older adults to contribute to society [22]. PVs will be recruited from a pool of regular members in the IAA. The IAA staff will announce and promote this study to those members. Those members who are interested will be invited to register and participate in the study. A total of 30 will be recruited. It is assumed that older adults who apply for membership in the IAA are active and willing to become involved in group activities. IAA members who express an interest will attend a selection interview. The selection criteria for the PVs include: ≥50 years old, retired, has a positive attitude towards aging and peer support, committed to completing two training workshops, passes the knowledge test, is able to demonstrate the use of a booklet among peers after the training workshops to the satisfaction of the research team, and is willing to provide services after the training. Retirees will be chosen, as their schedule is assumed to be more flexible, allowing them to arrange the time to volunteer.

### Training for peer volunteers

Prospective PVs will attend two **
*training workshops*
** prior to the 8-week group-based IPMP. They will be informed on the procedure of the program, the correct way to implement a variety of exercises and multisensory therapy, communication skills, and personal safety. Exercises and examples of multisensory therapy will be demonstrated to them. They will also be instructed to pair up with one another and to role play. The trainers will be the Principal Investigator and the research team. The content of the training will be validated by the Principal Investigator and the research team.

### Roles of peer volunteers

The PVs will work with the research team to develop the ‘I can do it’ booklet. They will contribute ideas for the content of the booklet. This will help to increase their knowledge, satisfaction, and compliance with the program. The PVs will then act as facilitators in the 8-week IPMP. Session 1 of each week will include 30 minutes of interactive teaching and sharing, 20 minutes of exercise, and 10 minutes of making entries in and reviewing the ‘I can do it’ booklet. The PVs will visit the nursing home with the research assistant in session 1 and assist in guiding the participants to do exercises and carry out the activities. Within the same week, session 2, which includes 30 minutes of revision, 20 minutes of exercise, and 10 minutes of entry and reviewing the ‘I can do it’ booklet, will be conducted by the PVs only. The content that the participants covered in the previous session will be revised and any remaining arts and crafts activities will be continued. It is expected that the participants will develop a habit of exercising and using non-pharmacological methods of pain relief after regular reminders and accompaniment by the PVs. The PVs will also be responsible for following up on the participants after the 8-week IPMP by visiting them weekly during weeks 9 to 12 to remind them to do their exercises and apply non-pharmacological strategies.

### Support for peer volunteers

The research team will be present in session 1 of each week and will share information and teaching experiences with the PVs. During session 2 of the first two weeks, the research team will observe the PVs facilitate the sessions and provide feedback at the end of the session. Any difficulties that are encountered will be discussed, mutual support and encouragement will be provided, and recognition of the achievements of the PV will be given to enhance their satisfaction. PVs can also call the research team for prompt support when necessary. A guidebook for PVs will also be developed as a reminder for the PVs.

### Measures of the quality of the peer volunteers

Guidebooks will be given to the PVs as guidance for practice so that they will be able to work independently according to the standard protocol. In assessing the PVs in terms of their adherence to the study protocol, the PVs will be required to pass a knowledge test and demonstrate the use of the booklet among their peers to the satisfaction of the research team after the training session and before they facilitate the sessions. The PVs will also be required to participate in session 1 of each week. A monitoring system will be put in place to allow the research team to observe the PVs during the first two weeks and to discuss with the PVs any issues that might arise.

Eligible participants and peer volunteers will be given written information about the study and required to return a consent form.

### Ethics committee

This project has already obtained ethical approval from the Departmental Research Committee of The Hong Kong Polytechnic University (Reference Number: HSEARS20140124002).

### Study design

#### Procedure

As in Figure 1, the following data will be collected on the participants at P0 (baseline, that is, before the IPMP): demographic data (age, gender, marital status, medical history, educational level), pain score, functional mobility, physical activity, loneliness level, happiness level, and use of non-pharmacological pain management methods. An 8-week group-based IPMP during weeks 1 to 8 will then be offered. Each session will involve a group of 15 participants. To detect the dose-response relationship, pain scores will be collected at the beginning of each session from weeks 1 to 8 (P1). At week 8 (P2) and week 12 (P3), the following data will be collected: pain score, functional mobility, physical activity, loneliness level, happiness level, and use of non-pharmacological methods to relieve pain.As in Figure 2, PVs will complete the questionnaire for volunteers at four time points, that is, before the training (V0), after the training (V1), at week 4 (V2), and at week 12 (V3).

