## Method/Design

### Design

It will be a single group trial.

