### Outcome assessment

#### Primary outcome

The primary outcome measure is pain intensity, which will be assessed using an 11-point numeric rating scale (NRS). The NRS is a line marked in equal segments from 0 (no pain) to 10 (worst possible pain). The NRS has been shown to be a reliable and valid measure of pain intensity and pain distress in older patients with persistent pain [23].

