## Discussion

The 8-week group-based IPMP has already been validated and published, and its effectiveness has been established. Interventions that include some type of social support have great potential to increase participation and adherence, raising the question of whether the effects of an IPMP can be extended with the use of PVs. This study is aimed at evaluating the feasibility of using PVs in an IPMP for Hong Kong older adults with chronic pain.

This pilot study helps older adults to control their pain by providing a PV to encourage and accompany them. The limitations of this study should be noted. As it is only a pilot study lasting 12 weeks, long-term changes in the outcome measures cannot be evaluated. Moreover, there may be a ‘learning effect’, which will familiarize the participants with measuring instrument in the study as there will be a repeated measure of pain intensity in the beginning of all 16 training sessions. This study provides evidence for future, larger studies that utilize a randomized controlled design and a possibly longer follow-up time to adjust this ‘learning effect’ and to investigate whether PVs should be integrated in programs for older adults with chronic pain. This will help to promote health among older adults in the long term.

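### The session-1 pain score precedes any programme content but is labelled on-programme P1; it belongs in the baseline, for a precision gain of uncertain size (at most 25% for a change to week 8 or 12 if readings are equally correlated)

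*Protocol article*

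**What the plan says.** The Protocol article describes an uncontrolled pilot: "It will be a single group trial", and "The present study will be a pilot study with 30 participants". The primary outcome is pain on a 0-10 scale: "The primary outcome measure is pain intensity, which will be assessed using an 11-point numeric rating scale (NRS".

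The Procedure section places one pain score "at P0 (baseline, that is, before the IPMP". It then adds the session series, kept for the dose-response question: "pain scores will be collected at the beginning of each session from weeks 1 to 8 (P1". The Discussion confirms that no session is left out, since it refers to "a repeated measure of pain intensity in the beginning of all 16 training sessions". Pain is scored again at week 8 (P2) and week 12 (P3).

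The Data analysis section counts P1 as one of four time points. For pain it lists t-tests of P0 with P1, P1 with P2, and P1 with P3. The comparisons of P0 with P2 and P0 with P3 are assigned to the other variables. The same section plans a GEE with quadratic and higher terms for dose-response. It does not say how 16 session readings become one P1 value, nor how dose is coded.

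**The concern.** A score taken at the start of session k reflects k-1 completed sessions. At session 1 that is zero, so the first P1 reading has the same exposure as P0. Counting it as on-programme places an untreated value in the treated side of P0-P1 and in the comparator for P2 and P3.

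Two things are at stake. The first is what the pain tests estimate: P0-P1 is slightly diluted, and the week-8 and week-12 results are set against an average taken during the programme instead of a value from before it. The second is precision. Baseline pain rests on one reading in people whose pain may be present "either all the time or on and off for more than three months", with only 30 participants, while a second pre-intervention reading is already being collected and is not used as one.

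**Working it through.** The article states no effect size, SD, correlation or power, so there is no figure of its own to reproduce.

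**Inputs from the article:** 30 participants; one P0 reading; 16 session readings; single readings at P2 and P3; significance level 0.05.

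**Assumptions:** P1 is the mean of the session readings; all readings have variance s²; r is the correlation of either baseline with a later reading; rb is the correlation between the two baselines; tests are two-sided and paired.

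**1. Dilution of P0-P1.** One of 16 readings carries no effect, so the mean of 16 shows 15/16 of the mean effect over the other 15. The loss is 1/16 = 6.25%.

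**2. What P1-P2 measures.** Suppose, for illustration, that benefit builds in proportion to sessions received and that P2 follows all 16. Mean exposure within P1 is (0+1+...+15)/16 = 7.5 sessions, so P1-P2 spans 16 - 7.5 = 8.5 of 16 sessions, about 53% of the effect. Dropping session 1 from P1 raises its mean exposure to 120/15 = 8 sessions. Removing the reading therefore does not repair P1-P2; the comparator has to change.

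**3. Change from baseline to P2 or P3.**
- One baseline: variance = 2s²(1-r).
- Mean of two baselines: variance = s²[1 + (1+rb)/2 - 2r].
- Proportional cut = (1-rb)/[4(1-r)].

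If rb = r, the variance falls from 2s²(1-r) to 1.5s²(1-r), a 25% cut. With r = 0.5:

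| rb | 0.5 | 0.6 | 0.7 | 0.8 | 0.9 |
|---|---|---|---|---|---|
| cut | 25% | 20% | 15% | 10% | 5% |

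Illustrative time-decaying structures, with P0 assumed one week before session 1, give cuts for P2 of about 8% (pure AR(1), weekly correlation 0.90 or 0.95), 14% to 17% (person effect, AR(1) and noise) and 22% (mostly person effect and noise).

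**4. The listed P0-P1 contrast, equal correlation, in units of s²(1-r).**
- As planned: 1 + 1/16 = 1.0625.
- Two baselines against the mean of 15: 1/2 + 1/15 = 0.5667.
- Ratio 0.533, a 46.7% cut. The time-decaying structures give about 13% to 42%.

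**5. The listed P1-P2 contrast, same units.** Removing session 1 moves the variance from 1.0625 to 1 + 1/15 = 1.0667, a 0.4% rise, so nothing is gained there.

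**6. Power (noncentral t, n = 30).** 80% power needs a standardised change of 0.529. For the same true change:
- 5% cut: 82.0%.
- 10% cut: 84.0%.
- 25% cut: 0.529/√0.75 = 0.611, power 89.9%.

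**The case against.** The best defence is that this is a feasibility pilot, that reducing 16 readings to one P1 is analysis-plan detail, and that the GEE needs a zero-exposure anchor. Much of that stands. That the readings are pooled is an inference, and the session-1 score is useful in the GEE. But the article itself fixes the label, the timing and the contrasts, and together these put an unexposed score in the on-programme time point.

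Several stronger readings are tempting and are not supported:

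- **A flat 25% gain, or 30 participants worth 40 (30/0.75).** A reader might infer this from the equal-correlation algebra. It needs the two baselines to correlate no more with each other than with readings 8 to 12 weeks later. The article gives no correlations and no interval between P0 and session 1. The 25% also applies to a pain contrast that is not currently listed.
- **A gain over the listed P1-P2 test.** Under equal correlation a two-baseline change to P2 has variance 1.5s²(1-r), above the 1.0625s²(1-r) of P1-P2. The case for it is that it measures change from before the programme; the saving is relative to a single-baseline change.
- **A mis-coded dose scale.** No coding is stated. With lower-order terms kept, coding session k as k or k-1 only shifts the origin of the polynomial, and the fitted curve is the same.
- **Serious regression to the mean.** The Participants section sets no minimum pain score, so people are not selected on a high P0 reading and the usual mechanism is absent.
- **An underpowered primary test.** The article makes no power claim; the 80% starting point above is only a reference.

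The Discussion's warning of a learning effect also stands: the second reading may be slightly affected. That is equally so if it stays in P1.

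**Conclusion.** The point holds in limited form. The session-1 pain score is pre-intervention by the article's own timing and should not be part of on-programme P1. Pain at weeks 8 and 12 has no listed comparison with a pre-intervention value.

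The dilution of P0-P1 is about 6%, if P1 is a mean of 16. The precision gain is real in every structure examined for the baseline contrasts, but its size is unknown: about 5% to 25% of the variance of a baseline-to-P2 or P3 change, and at most about 47% in those structures for P0-P1. These figures rest on assumed correlations and on equal variances. This is an inexpensive improvement worth making, not a defect that invalidates the pilot.

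**What to change.** Before the data are examined, change the wording of the Procedure and Data analysis sections as follows:

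1. Define the week-1 session-1 pain score as pre-intervention, and require it to be taken before any session content and before the booklet is handed out. The booklet section places that handout at the start of the programme, so the order needs stating.
2. Define baseline pain as the mean of P0 and that score.
3. Start on-programme P1 at session 2, and say how its 15 readings become one value.
4. Add comparisons of pain at P2 and at P3 with this baseline.
5. Keep the session-1 score in the GEE as the zero-exposure point, and state dose as sessions already received (0 to 15). This is a clarification and does not alter the fitted curve.
6. If the precision gain is mentioned, give it as a range with its correlation assumptions.

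The cost is wording only, since both readings are already collected. There are two small downsides. The pain baseline will differ from the single-reading P0 used for the other outcomes, and the learning effect may touch the second reading. Repeating the pain comparisons with P0 alone would show whether either matters.

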**Figure 1 F1:**
[figure not shown]
Research study design for participants.

**Figure 2 F2:**
[figure not shown]
Research study design for peer volunteers.

#### Preparation of the booklet and relevant materials

The booklet and other relevant materials will be prepared as indicated below:

1. ‘I can do it’ booklet. A booklet will be given to each participant at the beginning of the IPMP, and they will be asked to bring this booklet to all sessions. The booklet summarizes the key points of pain management strategies learned in the program and demonstrates the steps of various types of exercises. This booklet of each participant will be stamped every time they participate in a session. Outside the classroom, the booklet will also be used to record their participation in exercises or their application of other non-pharmacological methods. The booklet will be validated by the research team.

2. Materials for the IPMP. Various class materials will be delivered in the IPMP. Materials include music CDs for participants to listen to when they practice deep breathing; herbal tea to stimulate their taste buds; and scissors, glue, origami paper, and colorful art materials for the arts and crafts therapy to facilitate fine motor activities. All of the materials will be kept in the nursing home for the PVs to use until the end of the study.

3. Guidebook for peer volunteers. A guidebook will be developed for the PVs to ensure that the procedure and content of each session are standardized. Safety and privacy issues will also be mentioned in the guidebook. Links to webpages on pain management strategies will be printed for their reference. The guidebook will also include guidelines on how to use the ‘I can do it’ booklet. The guidebook will be validated by the research team, as well as by an advanced practice nurse, consultant, and physiotherapist from the Pain Clinic.

#### Evidence-based practice: Integrated pain management program (IPMP)

The participants will be given an 8-week group-based IPMP supplemented with PVs. Table 1 shows the details of the IPMP. We will follow the study design of a previous study [7]. There will be 16 sessions, with two 1-hour sessions each week.

**Table 1 T1:** Integrated pain management program (IPMP)

**Week**	**Session 1**			**Session 2**		
	**(research assistant and peer volunteers)**			**(peer volunteers only)**		
	Interactive teaching and sharing	Exercise	Entry	Revision	Exercise	Entry
		(20 minutes)	(10 minutes)	(30 minutes)	(20 minutes)	(10 minutes)
	(30 minutes)					
1	Introduction on pain	Deep breathing	Research assistant and PVs will work together with the participants to make entries in the ‘I can do it’ booklet on the activity of the day.	PVs will use the ‘I can do it’ booklet to review the content taught in the previous session and continue any remaining arts and crafts activities.	Deep breathing	PVs will work together with the participants to make entries into the ‘I can do it’ booklet on the activity of the day.
	Impact of pain					
	Drug therapy					
2	Hot pad and cold pad	Relaxation exercise			Relaxation exercise	
3	Music therapy	Warm-up exercise			Warm-up exercise	
4	Massage	Shoulder and neck exercise			Shoulder and neck exercise	
5	Use of five sensations as nondrug therapies: making a photo album	Lower arm exercise			Lower arm exercise	
6	Use of five sensations as nondrug therapies: making a bag of dried flowers	Towel dancing			Towel dancing	
7	Use of five sensations as nondrug therapies: tasting of tea	Towel dancing			Towel dancing	
8	Wrapped up	Whole body exercise			Whole body exercise	

Session 1 of each week aims to empower the older adults with knowledge of how to manage pain and to demonstrate the procedure of the selected exercise. The research assistant (RA) will lead the sessions and the PVs will help the RA to guide the participants in doing exercises and assist them in carrying out the activities. Session 1 includes:

1. 30 minutes of interactive teaching and sharing. The contents include an introduction on pain, the impact of pain, drug therapy, five sensation therapy (touch, smell, taste, hearing, and vision), making a photo album and bags of dried flowers, and a tea tasting.

2. 20 minutes of exercise. Specific exercises for the shoulder, neck, arms, and the whole body, and balancing and towel dancing will be taught.

3. 10 minutes of making entries and reviewing the ‘I can do it’ booklet.

Session 2 of each week will be led by the PVs only. It includes:

1. 30 minutes of reviewing what the participants learned in the previous session and continuing any remaining arts and crafts activities;

2. 20 minutes of exercise to help them to develop it as a habit; and

3. 10 minutes of making entries and reviewing the ‘I can do it’ booklet.

### Outcome assessment

#### Primary outcome

The primary outcome measure is pain intensity, which will be assessed using an 11-point numeric rating scale (NRS). The NRS is a line marked in equal segments from 0 (no pain) to 10 (worst possible pain). The NRS has been shown to be a reliable and valid measure of pain intensity and pain distress in older patients with persistent pain [23].

#### Secondary outcomes

Functional mobility will be measured by Timed Up and Go Test [24]. The participants will be required to walk a distance of three meters, turn, walk back to the chair, and sit down. It is a short test of basic mobility skills. Participants who can finish the test within ten seconds will be interpreted as having normal mobility. Those who can do it in 11 to 20 seconds will be interpreted as having good mobility and not requiring a gait aid. Those who require 21 to 30 seconds to complete the test will be regarded as having problems with their gait and requiring a gait aid. The participants will be instructed to do the test with their usual footwear. There will be no time limit for the test. The RA will stay beside the participants during the test for timing and safety purposes. The test-retest reliability of this test is 0.97 [25]. A practice trial will be given and the test will be performed once with time recorded [26].

Physical activity will be assessed from the notes in the ‘I can do it’ booklet as well as from the results of the Global Physical Activity Questionnaire (GPAQ) developed by the World Health Organization. The GPAQ consists of several components of physical activity including intensity, duration, and frequency. It has been shown to be valid and reliable, and also adaptable to the incorporation of cultural differences [27].

The use of non-pharmacological methods will be recorded in the ‘I can do it’ booklet. The frequency of the use of non-pharmacological methods will be counted as the number of times per week without considering duration, as we simply want to provide tools for the older adults to manage their pain. The participants will be asked to tick the boxes for the corresponding pain-relieving method whenever they apply (for example, listening to music, deep breathing, and smell stimulation).

The loneliness level of the participants will be measured using the Loneliness Scale [28]. The scale consists of 20 items to assess the participants’ perception of loneliness and social isolation using a 4-point Likert scale (1 = never, 2 = seldom, 3 = sometimes, 4 = always). The total possible scores range from 20 to 80, with higher scores indicate greater loneliness. The Chinese version will be used with a Cronbach’s alpha of 0.9 [29].

The happiness level of the participants will be assessed by the Chinese version of the subjective happiness scale [30]. It consists of four items rated on a 7-point Likert scale. The total scores range from 4 to 28, with higher scores indicate higher subjective happiness. The Cronbach’s alpha is 0.79 to 0.94. The test-retest reliability ranges from 0.55 to 0.90 [30].

The questionnaire for volunteers, which contains open-ended and closed questions, will be completed by the PVs. Closed questions include those on their self-efficacy in learning and implementing the IPMP, self-rated knowledge of pain management; rating of the training, satisfaction with the program, and skills in delivering it. Examples of open-ended questions include attitudes and prior experiences of involvement in voluntary programs for older adults, expectations of the program, perceptions of various aspects of the program, and perceptions of barriers to and facilitators of the program.

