#### Data analysis

The IBM-SPBB version 20 will be used to perform a statistical analysis. Descriptive statistics (frequency, %), mean (standard deviation)) will be used to describe the demographic data of the participants.

To determine the dose-response relationship of this intervention program on pain, a generalized estimating equation with quadratic and higher order terms will be used. To examine the intervention effect, a t-test will be used to compare the mean pain intensity, functional mobility, physical activity, loneliness and happiness levels, and use of non-pharmacological methods collected at four time points, that is, between P0 and P1, P1 and P2, P1 and P3 (for pain only), and between P0 and P2, P0 and P3, and P2 and P3 (for other variables). The Kolmogorov-Smirnov normality test will be used to examine the normality of the outcome variables. If the data do not follow a normal distribution, we will use the Wilcoxon Signed-rank test and the Mann-Whitney U test for within-group and between-group comparisons, respectively. A *P* value of <0.05 will be considered statistically significant. An intention-to-treat analysis will be conducted for any missing data. All data from the ‘I can do it’ booklet will be gathered and used to calculate the participation rate.

The questionnaires for the volunteers will be compared using the McNemar test and a pair sample t-test for quantitative data. Qualitative data will be analyzed using content analysis [31]. Sentences or parts of sentences will be identified as meaningful units in each questionnaire. The meaningful units will be categorized into themes related to the perception of program. The themes will be compared and discussed to establish the credibility of the interpretations.

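### Use of non-pharmacological methods has no comparable baseline: its only named instrument, the booklet, is issued when the programme starts, and the week-8 count may include the sessions themselves

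*Protocol article*

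**What the plan says.** All references are to the protocol article.

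- **Schedule (Procedure).** Baseline is defined as "P0 (baseline, that is, before the IPMP"). The outcomes listed there include "loneliness level, happiness level, and use of non-pharmacological pain management methods". The same outcome is collected again at week 8 (P2) and week 12 (P3).
- **Instrument (Secondary outcomes).** "The use of non-pharmacological methods will be recorded in the ‘I can do it’ booklet". The frequency "will be counted as the number of times per week without considering duration", from boxes that participants tick. No other instrument is named for this outcome.
- **Issue of the booklet (Preparation of the booklet and relevant materials).** "A booklet will be given to each participant at the beginning of the IPMP". Exercise and other methods used outside class are also entered in it.
- **Entries in sessions (Table 1).** In both weekly sessions, participants are helped to enter that day's activity: by the research assistant and volunteers in session 1, and by the volunteers alone in session 2.
- **Physical activity (Secondary outcomes).** "Physical activity will be assessed from the notes in the" booklet, and also from the Global Physical Activity Questionnaire (GPAQ).
- **Tests (Data analysis).** For outcomes other than pain, means are compared "between P0 and P2, P0 and P3, and P2 and P3 (for other variables").
- **Design.** Single group, 30 participants, described as a pilot.

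**The concern.** A before-after comparison in one group can be read only if the outcome is measured in the same way on both occasions. Here the stated instrument does not reach participants until after the first occasion, so two of the three planned tests for this outcome cannot be run as described. If P0 is filled by recall or interview and P2 by an assisted tick record, the difference mixes a change in behaviour with a change in method.

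A second problem adds to this. If ticks made in sessions count as use, part of the week-8 value is attendance at the programme. P0 to P2 could then rise without any change in what residents do on their own, and P2 to P3 could fall because the sessions have ended.

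Use of these methods is part of the stated hypothesis, and the results are meant to inform whether a larger randomized trial is needed. There is no control arm in which the artefact would show or cancel. Once P0 has passed, a baseline can no longer be collected prospectively.

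**Working it through.** **1. Timing of the instrument.** The article gives no effect size, standard deviation or power for this outcome, so there is no figure to reproduce. The check sets four statements side by side:

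| Statement | Section |
|---|---|
| Outcome required at P0, before the programme | Procedure |
| Outcome measured by the booklet | Secondary outcomes |
| Booklet handed out when the programme begins | Preparation of the booklet |
| P0 tested against P2 and P3 | Data analysis |

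The first three cannot all hold: the booklet cannot supply a P0 count. This step needs no assumption.

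**2. What the week-8 count may contain.** There are 2 sessions a week (8 x 2 = 16, which agrees with the stated total). Each has one exercise and a slot for assisted entries on the day's activity. In week 8 the exercise is a whole-body one and the teaching slot is a wrap-up with no new method. Some session content is countable: deep breathing is both a tick-box example and the week 1 exercise. The article does not say whether the week 8 exercise has a box, or whether session ticks count. Assuming that it has, that they count, and that attendance is full:

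2 sessions x 1 ticked exercise = 2 entries per week.

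With partial attendance or partial ticking, the figure is lower. If session ticks are excluded, it is 0.

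**3. Chance of P<0.05 from the artefact alone.** Two-sided paired t-test (sidedness assumed), alpha 0.05, n = 30, 29 degrees of freedom. For a mean artefact d and a standard deviation s of the paired difference, the noncentrality is (d/s) x √30. For d = 2 and s = 3, for example, it is (2/3) x 5.477 = 3.65, and the probability is 0.94. Both d and s are assumptions; the documents give neither.

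| Artefact d (per week) | s = 2 | s = 3 | s = 4 | s = 6 |
|---|---|---|---|---|
| 2 | 1.00 | 0.94 | 0.75 | 0.42 |
| 1 | 0.75 | 0.42 | 0.26 | 0.14 |
| 0.5 | 0.26 | 0.14 | 0.10 | 0.07 |

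The nominal rate is 0.05. The planned fallback to the signed-rank test would not help, because it compares the same contaminated differences.

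**4. Which comparisons are affected.**
- P0-P2: change of instrument, and possibly session entries at P2.
- P0-P3: change of instrument only. The sessions have ended; only weekly volunteer visits remain in weeks 9 to 12.
- P2-P3: same instrument at both times, but possible loss of session entries.

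**5. Physical activity.** The booklet notes lack a baseline for the same reason. The GPAQ does not depend on the booklet and can be given at all three times.

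**The case against.** The strongest reply is that the main defect is narrow. A P0 value is planned, and an article may leave the baseline form to the full protocol. The outcome is secondary, the trial is a 30-person feasibility pilot, and the primary outcome, pain on the numeric rating scale, is untouched. Attendance has its own record, a stamp in the booklet, so ticks may be meant only for self-directed use. For physical activity, the GPAQ already offers a comparable series.

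Most of this stands, and it lowers the severity. It does not remove the conflict: the article does name an instrument, and that instrument does not exist for participants at P0.

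A reader might also infer more than the text supports:
- **Four built-in entries per week, from a taught method plus the exercise.** Week 8 teaches no new method. Even 2 is not a guaranteed minimum, since it rests on an unstated counting rule.
- **A significant P0-P2 result is almost certain.** This depends on the assumed standard deviation and artefact; the table runs from 1.00 down to 0.07.
- **Session entries also inflate P0-P3.** There are no sessions in week 12.
- **Nobody helps with entries after week 8.** Volunteers visit weekly in weeks 9 to 12, and the article does not say whether they help with the booklet.
- **The week-8 GPAQ is contaminated by supervised exercise.** The documents give neither its recall window nor a counting rule. Supervised exercise is also real activity, so leaving it out would be a choice of what to estimate, not the correction of an error.

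**Conclusion.** The concern holds in two parts. The first is certain: the named instrument cannot supply the P0 value for use of non-pharmacological methods, so P0-P2 and P0-P3 compare different measurements, and a single-group design cannot remove the difference. The second is possible: with no rule excluding session entries, the week-8 count may be raised by up to about 2 per week, and a P2-P3 fall may partly reflect the end of the sessions. At that upper figure, a false significant P0-P2 result has a probability between 0.42 and 1.00 over the assumed standard deviations of 6 down to 2, and less for smaller artefacts. For physical activity, only the booklet-based part is affected. Severity: should be fixed, since the outcomes are secondary and the study is a pilot.

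**What to change.** - At P0, P2 and P3, have the research assistant complete the same past-week checklist: how many times each method was used outside programme sessions. Use it for the three planned comparisons.
- Name the GPAQ as the physical-activity measure that is tested.
- Keep the booklet data to describe participation and adherence.

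The cost is a one-page form at three assessments that already take place. The downside is some recall error in place of diary counts, but the same method then applies at every time point. The form must be in place before P0 is collected.
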